		Which contextual factors do they consider important when working with PAP?
3	Evaluation of PAP for children with obesity on implementation and clinical outcomes — a single-arm intervention study	Do healthcare professionals’ and managers’ perceptions of PAP and working with PAP for children with obesity change after a PAP intervention?
		Do physical activity patterns of children with obesity and one of their parents change after participation in a PAP intervention?
		Is there a correlation between the child’s and their parent’s physical activity pattern?
		Is there a change in BMI, metabolic risk markers, health-related quality of life, sleep, or self-efficacy or motivation for physical activity after participation in a PAP intervention?
		What is the acceptability and feasibility of the intervention among children and parents?
4	Children’s and parents’ experiences of participating in a PAP intervention — an interview study	What are the experiences of children with obesity and their parents of participating in a PAP intervention?
		Which barriers and facilitators of implementing PAP do children and their parents perceive?
		How do children and parents perceive their (their child’s) behaviour change, if any, with particular emphasis on physical activity behaviour?

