For the assessment of clinical outcomes in study 3, we aim to recruit approximately 60 children with obesity who have been prescribed PAP and one of their parents/guardians from the paediatric clinics in Gothenburg and surrounding communities who agree to participate. Because this is a feasibility study, we have not undertaken a formal sample size calculation but aim to include a sufficient number of participants to provide information about practicalities such as recruitment and attrition rates, intervention fidelity, dose, and adherence, as well as for statistical analyses of clinical outcomes. We have also given consideration to the likelihood of a fairly large attrition rate at each time point. Uncertainties about the recruitment procedure, the capacity to achieve an appropriate sample size, and the intervention itself will be considered in terms of feasibility and whether it is of value to proceed to full-scale evaluation. Children and parents will be screened for eligibility by the staff at the participating paediatric clinics in conjunction with their first visit. All who meet the inclusion criteria will be given oral and written information about the study and asked about interest in participating. Inclusion criteria are as follows: being aged 6–12 years, diagnosed with obesity (BMI > ISO-BMI 30), having an insufficient physical activity level according to national recommendations, and having a parent who is willing to participate. Insufficient physical activity level is defined as not reaching the national guidelines recommendation of 60 min of moderate to vigorous physical activity per day [12]. Exclusion criteria are as follows severe psychiatric comorbidity, severe intellectual or physical disability, or planning to relocate outside the study area within 12 months. To support recruitment and reach the desired sample size, site coordinators will be appointed, trained, and provided with adequate study material.

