#### Clinical outcomes

All clinical outcomes will be measured pre- and post-intervention and at 8 and 12 months’ after baseline. The primary clinical outcome will be physical activity level, measured as minutes per day spent in moderate to vigorous physical activity (MVPA) and assessed using the Axivity accelerometer (Axivity AX3, Axivity Ltd., UK). Accelometry is the most commonly used method in clinical and epidemiological research for objective measurement of physical activity, is easy to use for the study participant and the researcher, and has a high sensitivity for detecting changes in physical activity (30). The accelerometer will be placed above the child’s and parent’s hip in an elastic belt and worn 24 h per day for seven consecutive days. In this position, the accelerometer can be used to assess physical activity at different intensities. The accelerometer recording is accompanied by an activity diary to determine bedtime, non-wear time, and sport activities. A strict protocol for data quality assurance (malfunction, spurious data, wear time, valid days) will be used. A project coordinator will provide the accelerometer to the participants together with oral and written instructions, support the participants if necessary, and collect the accelerometer after use. Measurement procedure, quality assurance, data processing, and analysis will be supported by an experienced team at the Center for Health and Performance [58].

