Secondary clinical outcomes will be physical activity patterns (time spent in different types of activities and at different intensity levels, including sedentary time) measured with accelerometry; anthropometric measures, i.e. BMI; and waist circumference, collected from medical charts. Metabolic risk markers will be assessed via blood pressure measures and blood samples, including fasting plasma glucose, high- and low-density lipoprotein cholesterol, insulin resistance, and triglycerides. In addition, patient-reported health-related quality of life will be measured using KIDSCREEN-10 [59], and the child’s sleep will be measured using the Insomnia Severity Index (ISI) [60, 61]. Parents’ perception about their child’s sleep will be measured using the Pediatric Insomnia Severity Index (PISI) [62, 63]. The child’s self-efficacy for physical activity, and motivation for physical activity, will be measured with validated instruments adapted to children with obesity and parents and appropriately translated to Swedish [64–67]. Adverse events will be monitored and documented.

Demographic data on children will be collected at baseline, including age, gender, comorbidities, and country of birth. Data on participating parents/guardians include age, gender, BMI, comorbidities, country of birth, and education level.

To enable missing data analysis, demographic data will also be collected for those who decline participation, when possible.

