#### Clinical outcomes

Descriptive statistics will be used to summarise characteristics of the participants and will be presented as means with standard deviations or frequencies and percentages. For physical activity outcomes, raw accelerometer data will be processed and filtered in several steps to a measure of activity intensity (mg) [58]. Previously developed and tested calibration equations for body positions, activity type, and for activity intensities will be applied [70, 71]. Accelerometer data will be analysed in 3-s epochs in order to accurately detect normal variation in physical activity [58]. Continuous data on physical activity patterns at baseline, 4, 8, and 12 months, will be analysed using multivariate regression analysis for repeated measures, controlled for multicollinearity between intensity levels. To examine potential influences of demographic and parental factors (gender, age, education level, country of birth) on physical activity patterns, the models will be adjusted for these variables. Change in absolute BMI in kg/m^2^ and in metabolic risk markers in mmol/L will be calculated and analysed using mixed linear modelling. Standardised measures for the separate risk factors waist circumference, insulin resistance, systolic and diastolic blood pressure, high-density lipoprotein, and triglycerides will also be combined in a so-called MetS score and analysed using mixed linear modelling. Patient-reported outcomes will also be analysed using mixed linear modelling and adjusted for the same demographic and parental factors. Changes over time will be presented with 95% confidence intervals. The self-efficacy and motivation variables’ potential mediating role for physical activity will also be explored by including these parameters into the models as covariates. Statistical significance will be set at *p* < 0.05.

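### BMI change is analysed in absolute kg/m² in growing children with no control group, so expected growth and any intervention change fall into the same time coefficient

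*Protocol article*

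**What the plan says.** All points are in the protocol article.

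- **Population** (Recruitment of study participants and sample size): children "being aged 6–12 years, diagnosed with obesity (BMI > ISO-BMI 30"), about 60 of them, with no formal sample size calculation.
- **Design** (Study design): one group, measured before and after, with no comparator.
- **Visits** (Data collection and outcomes, Clinical outcomes): "All clinical outcomes will be measured pre- and post-intervention and at 8 and 12 months’ after baseline". The intervention lasts 4 months, so the visits are at 0, 4, 8 and 12 months.
- **Role of BMI** (same section): a secondary outcome, listed as "anthropometric measures, i.e. BMI; and waist circumference, collected from medical charts". The primary clinical outcome is accelerometer-measured minutes of moderate to vigorous activity.
- **Question** (Table 1, study 3): "Is there a change in BMI, metabolic risk markers, health-related quality of life, sleep, or self-efficacy or motivation" for physical activity after taking part.
- **Analysis** (Data analysis, Clinical outcomes): "Change in absolute BMI in kg/m^2^ and in metabolic risk markers in mmol/L", fitted with a mixed linear model. Changes over time come with 95% confidence intervals, and significance is set at 0.05. Adjustment for gender, age and other factors is stated for the physical activity models and for patient-reported outcomes. The BMI sentence has no such clause.
- **Limitation** (Strengths and limitations): the article says that the missing control group rules out conclusions about effectiveness. It does not mention growth.

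**The concern.** ISO-BMI 30 is a cut-off that depends on the child's age and sex. The protocol therefore uses an age-referenced scale to decide who has obesity, and an unreferenced scale to judge how that obesity changes while the same children become a year older.

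In a randomised comparison, growth would be common to both arms and would cancel. Here nothing cancels it. The time coefficient adds together what would have happened through growth and what changed through the intervention, and the data on this scale cannot separate them. Adding baseline age to the model would not separate them either: it adjusts for differences in level between children, while growth lies in the within-child change over time.

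At stake is the reading of a named outcome in an obesity study that is meant to inform a larger trial. The Discussion ties good prospects for routine implementation to positive results on physical activity and on other outcomes. A flat or rising BMI curve could be taken as absence of benefit when the children's age-relative position had improved.

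**Working it through.** The article gives no BMI effect, growth rate, SD of change or power figure, so there is no figure of its own to reproduce. The check is an illustration.

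**Inputs from the document:** n about 60; visits at 4, 8 and 12 months; significance level 0.05 (taken as two-sided, in line with the 95% intervals).

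**Assumptions (not in the document):** growth g in a child who keeps the same relative position, 0.3, 0.5 or 0.8 kg/m² per year; true intervention change e, 0 or −0.5 kg/m²; SD of individual change 1.5 kg/m², varied from 1.0 to 2.0; n = 42 as a case with 30% attrition.

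**Method:** one-sample t test of mean change from baseline, as a simple stand-in for the mixed model's time contrast.

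- Expected observed change = g × t + e, with t in years
- SE = SD/√n = 1.5/√60 = 0.194
- Chance of a significant result from the noncentral t distribution with n − 1 = 59 degrees of freedom and noncentrality (expected change)/SE

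**12 months, no intervention effect (n = 60, SD 1.5)**

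| Growth per year | Change/SE | Chance of a significant rise |
|---|---|---|
| 0.3 | 0.3/0.194 = 1.55 | 33% |
| 0.5 | 0.5/0.194 = 2.58 | 72% |
| 0.8 | 0.8/0.194 = 4.13 | 98% |

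**12 months, true relative improvement of 0.5 kg/m² (n = 60, SD 1.5)**

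| Growth per year | Expected observed change | Chance of a significant fall | Chance of a significant rise |
|---|---|---|---|
| 0 (growth removed) | −0.5 | 72% | <0.1% |
| 0.3 | −0.2 | 17% | 0.1% |
| 0.5 | 0.0 | 2.5% | 2.5% |
| 0.8 | +0.3 | <0.1% | 33% |

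**Sensitivity at 12 months, no intervention effect**

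- Growth 0.5, n = 60: 97% at SD 1.0 and 48% at SD 2.0.
- Growth 0.5, SD 2.0, n = 42: SE = 2.0/√42 = 0.309, ratio 1.62, chance 35%.
- Growth 0.3, SD 2.0, n = 42: ratio 0.97, chance 16%.

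**4 months (end of intervention), growth 0.8 per year, n = 60.** Expected change = 0.8 × 4/12 = 0.27.

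- If the SD of change is still 1.5: 0.27/0.194 = 1.38, chance 27%.
- If the SD shrinks with the square root of time: 1.5/√3 = 0.87, SE = 0.87/√60 = 0.112, ratio 2.39, chance 65%.

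The shift equals g × t whatever the SD or n. More children narrow the interval around the same shifted value and do not average it out.

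**The case against.** The strongest defence is about weight. BMI is one of many secondary outcomes, the primary clinical outcome is not touched, and the article discusses whether to proceed to full-scale evaluation in terms of recruitment, achievable sample size and the intervention itself, not BMI significance. The article also says openly that effectiveness conclusions are precluded. All of this stands and lowers the severity. It does not repair the scale: the disclosed limitation concerns causal claims and does not tell a reader that the BMI curve contains growth. Nor is the scale a detail left for an analysis plan, since the article itself fixes absolute kg/m².

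An upward drift also works against finding a benefit, so it would not manufacture a false claim of BMI reduction. That is correct; the risk is a missed improvement or an apparent worsening.

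Three stronger readings are tempting and are not supported.

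- A reader might infer that the analysis gives a wrong-signed answer. The question in Table 1 asks whether BMI changes, and change in kg/m² answers that literally and correctly. What fails is reading the number as change in obesity status or as an intervention effect.
- A reader might take the 98% figure as the size of the problem. It belongs to one assumed growth rate, one assumed SD and the 12-month visit. Other assumed values give 16% at 12 months, and 27% to 65% at 4 months for the same growth rate.
- A reader might extend the point to the metabolic composite, whose components "will also be combined in a so-called MetS score". The article says the measures are standardised but not against what. Both age- and sex-referenced and fixed-baseline standardisation fit the text, and an article commonly leaves such detail to the full protocol or analysis plan. No error can be shown there.

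**Conclusion.** The point holds for the scale of the BMI analysis and should be fixed; it is not critical to the study. In 6–12-year-olds followed for a year without a comparator, change in kg/m² mixes expected growth with any intervention change, and the protocol names no age- and sex-referenced change to set against it.

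The direction rests on one condition, that expected BMI rises with age in these children. The amount cannot be taken from the document. With 60 children and an SD of change of 1.5 kg/m², growth of 0.5 kg/m² per year would be enough to reduce the chance of seeing a true 0.5 kg/m² improvement at 12 months from 72% to 2.5%. That figure is an illustration under assumed inputs, not an estimate for this trial.

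**What to change.** In Data analysis, Clinical outcomes, make the BMI analysis that will be interpreted an age- and sex-referenced one, computed at every visit from the child's exact age on the day of measurement. Two suitable choices are BMI as a percentage of the child's own ISO-BMI 30 cut-off, or BMI SDS on a named reference. The first follows directly from the entry criterion. Keep the mixed model, and report change in absolute kg/m² alongside, with a sentence saying that it includes expected growth.

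The cost is a change of wording. Age and gender are already collected, and the ISO-BMI reference is already used at screening; only the date of each measurement needs to be at hand. The article already provides for important changes to be amended in the registry and reported in the publication. The one small drawback is a less familiar unit.

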#### Qualitative data

Data from the focus group discussions will be analysed using qualitative content analysis for focus groups [68]. A combination of inductive and deductive analysis will be used. Codes will first be developed inductively from the transcribed focus group sessions, and then, in a deductive approach using NPT as a coding framework, sorted into categories that reflect the four constructs of the NPT. Findings that cut across categories will be developed into one or several themes capturing the essence of the discussions and allowing for interpretation and a higher level of abstraction.

Data from the interviews with children and their parents will be analysed inductively using qualitative content analysis reflecting manifest and latent content of the interviews [69]. Meaning units of the transcribed interviews will be identified, condensed, and coded. Codes will be compared and, based on similarities, classified into categories and subcategories that describe the manifest content. Lastly, one or several overarching themes will be formulated based on the latent content that can be discerned across the categories.

### Ethical considerations and data management

In study 1, written participant information is provided via a link in the email that invites participants to answer the survey, and participants acknowledge having read the information and provide their consent by checking a box in the survey. In studies 2–4, written informed consent will be obtained from all participants. In studies 3–4, children and their parents/guardians will be provided oral and written information about the respective study, and informed parental consent and child assent will be obtained by the project coordinator or a site coordinator. Written information will be developed in a child version and a parent version. Because we consider it important to not exclude eligible non-Swedish-speaking children and parents, several language versions will also be developed, and interpreters will be available for those who do not speak Swedish or English.

A data management plan (DMP) has been developed, providing details on how data will be collected and managed throughout the project, as well as how they will be documented, stored, and archived after the project has been concluded. The DMP also contains information about how, when, where, and to whom data will be made available. The DMP can be provided on reasonable request from the principal investigator. Routines for data storage from Region Västra Götaland will be followed, and metadata standards will be used to describe the data material. A data management team will manage and monitor data accuracy and quality and comprises the principal investigator, the project coordinator/doctoral student, a postdoc researcher, and a research assistant. All study data, including the final study dataset, will be treated confidentially, and access will be restricted to the research team. When reporting findings, no data will be traceable to individual participants.

### Timeline

A timeline and schedule of enrolment, intervention, and assessments is presented in Table 2.

**Table 2 Tab2:**
[figure not shown]
Timeline of enrolment, intervention, and assessments

### Dissemination and implementation of study findings

The study findings will be reported in peer-reviewed scientific journals and social media and presented at seminars and national and international conferences. The results will also be disseminated through regular dissemination and communication channels, within and outside health care and university contexts. Summaries of results will be provided to the participants.

## Discussion

This research project investigates the feasibility of implementing physical activity on prescription to address childhood obesity, a global health issue of great and growing importance. The pre-implementation, hybrid design feasibility project was designed to evaluate the prerequisites, determinants, and feasibility of implementing PAP adapted to children with obesity and to explore the experiences of children, parents, and healthcare providers related to their experiences, attitudes, and perceived determinants for implementation. Implementation outcomes will be collected using questionnaires, based on validated instruments, before, during, and after a pilot implementation in participating paediatric clinics. Clinical outcomes will be collected from children and parents pre- and post-intervention and at 8 and 12 months from baseline. The process will be followed closely, and process evaluation data will be collected during and after the intervention. The project is expected to show whether PAP is a feasible intervention and has a place among other treatment options in paediatric health care.

The hybrid type-1 implementation-effectiveness approach is a useful design that allows parallel evaluation of the implementation process, preconditions, and determinants, as well as clinical outcomes [37]. It is particularly suitable in a context where the intervention is supported by evidence in one population but needs to be adapted and tested in another population while simultaneously assessing barriers and facilitators to “real-world” implementation of this intervention. This design is often used when testing an intervention in a randomised controlled trial design but can also be applied for the type of single-arm feasibility study in which an intervention is evaluated using a before-after approach. An important advantage of the hybrid design is that it could speed up the process of translating research findings into routine practice and allow for addressing many implementation research questions earlier than what could be achieved in a more traditional, linear “efficacy-effectiveness-implementation” approach [37]. The combination of outcome and process evaluation is particularly relevant in interventions that involve multiple stakeholders and, as in this case, partially is conducted in community settings where contextual factors will influence intervention outcomes [72].

Our choice of NPT as a theoretical framework for the project was based on its focus on the social processes surrounding the child, involving multiple stakeholders both within and outside the healthcare system. In addition to guiding implementation planning, its use also may help explain social processes related to implementing PAP in paediatric health care. The PAP intervention is complex and involves multiple healthcare professions and a range of other stakeholders, in addition to the child itself and their family. It also includes multiple processes that may be better understood through the lens of an implementation theory such as the NPT. Further advantages of using NPT is its empirical grounding in health care and its description as being stabile, robust, and user-friendly [73].

There is an abundance of measures to choose from when assessing implementation outcomes, with a varying range of psychometric quality [74]. We strived to select the most appropriate, relevant, and validated measures. The NPT-based S-NoMAD will be used to assess the implementation process, with a focus on the collective action employed in the different work processes involved in the treatment of children with obesity in the paediatric healthcare context. We chose the NPT constructs as primary implementation outcomes because they represent the mechanisms that shape the implementation process looking into a real-world setting, in this case a paediatric healthcare organisation. Furthermore, the S-NoMAD can be used to point out problems that can be addressed when implementing the intervention, as well as to assess the implementation process over time [37]. Supplementing S-NoMAD with the AIM, IAM, and FIM instruments will allow us to also assess implementation outcomes that are important determinants for implementation success. These outcomes have been proposed to be the most salient implementation outcomes to measure before the start of an implementation process in which an evidence-based practice is adapted and implemented [53]. The instruments are very brief, giving excellent usability, and have been rigorously developed and psychometrically tested [54].

A challenge when adapting a clinical intervention such as PAP that has been evaluated and found effective in another context is that adaptation by default means that intervention fidelity is not maintained [49]. Fidelity is considered important for implementation success [75] and an important part of a process evaluation [76]. However, a high degree of intervention fidelity requires strict adherence to a protocol and implies a top-down approach to implementation, whereas adaptation that involves engaging users and other stakeholders reflects a bottom-up approach [77]. This approach is not only more politically appealing from a social development perspective but is also likely to improve acceptability and feasibility of the intervention in the new context.

We chose physical activity level as primary clinical outcome because increasing physical activity is the main goal of the PAP intervention and because the effect of PAP on activity level has been established in adults [78]. We will assess physical activity objectively using accelerometers in this project as it reduces measurement errors associated with subjective methods, especially in children [58]. In addition, a robust measurement protocol will be applied to assure a high-quality standard, considering all steps from data collection to processing to achieve useful and reliable measures [58].

We will collect clinical outcome data immediately post-intervention and again at 8 and 12 months from baseline. It is well known that behaviour change takes time, and continued physical activity will be encouraged at the end of the intervention period. Conversely, it has also been shown that a positive change post-intervention, for example in BMI, may not be sustained in the long term [13].

PAP has already been used at several paediatric healthcare units, to varied extents, both in Region Västra Götaland and elsewhere in Sweden. This, together with the fact that PAP is a well-established intervention for adults, constitutes a clinical advantage and should facilitate a wider implementation of the intervention, if found effective, throughout the region and, later, to other regions in Sweden and potentially elsewhere. This project is expected to generate new knowledge regarding the feasibility of adapting PAP to children, as well as about whether and how an evidence-based intervention can be fitted and adapted to new contexts and populations. The qualitative study findings will increase our understanding of implementation determinants, including contextual factors, and of childrens’ and parents’ experience of participating in a PAP intervention. The study results may form the basis for a larger scale clinical trial, may guide future implementation, and may potentially enhance the role of physical activity in the management of obesity in paediatric health care in Sweden. If the adapted PAP intervention shows positive results on physical activity levels and other outcomes for the children included in this study, the prospects are good for implementing the intervention in routine paediatric health care.

